### Data collection

Data collection consists of self reporting questionnaires that are integrated in the portal. Therefore all data collection is provided digitally. In Fig. 6 the measurement schedule is visualized. There are four measurements in this study during a period of 16 months. Due to the ITS design, CCQs will be offered three times at each measurement.

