## Methods/Design

Our primary aim is to investigate the effect of use of patient portals on clinical outcomes in primary care COPD patients (net benefits, Fig. 1). In addition, we aim to investigate the optimal organisational implementation method of the platform. Therefore we will compare different organisational implementation methods in different care settings, and evaluate their use and user satisfaction. We hypothesize that an implementation setup with greater personal support, integrated into an existing care programme will be preferred by patients and therefore be more likely to be used.

As discussed in the introduction, the evaluation of eHealth is a challenge because of the different views to evaluate from (clinical, technical, and organisational). Moreover, eHealth is not a classical clinical isolated intervention (in this case a platform) with one output (here CCQ). Instead it affects care processes, communication and patients behaviour, Finally we have a multilevel purpose to not only investigate effects but also organisational implementation methods. Therefore we made a design for a quality improvement intervention. In this study we aimed to include the importance of integration in the daily practice of primary care. Therefore we chose an implementation study [25]. We designed a method to promote the uptake of our research findings into routine primary healthcare; with this design we aim at studying the influences on healthcare professionals and patient behaviour and at evaluating the process by which effects are achieved.

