##### Adoption of the portal

Usage of the portal is monitored continuously by log files. User satisfaction is measured by purpose-designed questionnaires.

From the organisational perspective we will measure the following outcome:

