##### Costs

In this study we include direct costs of the intervention and COPD care. Intervention costs include development costs of the patient platform and costs of the implementation process. Development costs are provided retrospectively by the owner of the portal. Implementation costs are administered by the research group and mainly include costs of home visits and interviews by telephone. The cost for COPD care (time of professional care) is extracted from the portal in which consultation in general practice will be registered in an agenda. In addition, hospitalisation (caused by COPD exacerbation) will be based on reports of the patient and practice nurse in the portal. All costs are based on regular tariffs in Dutch healthcare.

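### The primary CCQ is collected inside the portal under study, so follow-up can be lost differentially by support level and selectively over time

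*Protocol article*

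**What the plan says.** Under Data collection the article states "Data collection consists of self reporting questionnaires that are integrated in the portal" and continues "Therefore all data collection is provided digitally". There are four measurements, and "Due to the ITS design, CCQs will be offered three times at each measurement".

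Other outcomes come from the same system. Under Adoption of the portal, "Usage of the portal is monitored continuously by log files". Under Costs, the time of professional care "is extracted from the portal in which consultation in general practice will be registered in an agenda", and COPD admissions "will be based on reports of the patient and practice nurse in the portal".

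The trial also expects use to differ between the arms. Methods/Design hypothesises that a set-up with more personal support, built into an existing care programme, "will be preferred by patients and therefore be more likely to be used". The Discussion repeats the expectation for personal support. The Intervention section describes extra support in 1a and 2a that includes checking that patients can log on. Group 3 has no active support, no caregiver training and a portal that is not integrated in its disease management programme.

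Data analysis compares outcomes between high support (1a, 2a) and low support (1b, 2b, 3), and between integrated and free use, with (repeated measures) ANOVA among the methods. The power calculation assumes one drop-out rate, 20%, for every cell.

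**The concern.** The portal is both the intervention and the instrument that measures the primary outcome. A patient who stops logging in stops supplying CCQs. If support raises use, as the trial hopes, it also raises CCQ completion. The patients with data in 1a and 1b, or in 2a and 2b, are then no longer the balanced groups that randomisation created.

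The within-group time series is exposed in a second way. If patients who stop using the portal differ in health status from those who continue, the mix of patients behind the later waves changes. Part of any apparent change after the interruption may then be a change in who answers. No later analysis can recover CCQs that were never collected.

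Two further effects are possible: CCQ-driven sessions may count as usage, and care use and admissions may be recorded less completely where the portal is least embedded in practice.

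**Working it through.** **The plan's own figure.** Inputs from Power calculation: difference 0.5, SD 0.75, α = 0.05 (two-sided assumed), power 80%. The normal formula gives 2 × (1.96 + 0.842)² × (0.75/0.5)² = 35.3, so 36. The two-sample t-test version gives 36.3, so 37, which matches the stated 37 per cell. (37/0.80 is 46.25, not 45. That is a separate matter and does not affect this point.) With 45 enrolled and 20% lost in each arm, 36 remain per arm.

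**Bias in the support comparison.** Completion rates by arm are not in the documents, so these are assumptions. Let p be the proportion completing and g the amount by which non-completers score worse (a higher CCQ is worse). The completers' mean equals the true arm mean minus (1 − p) × g.

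- High support, p = 0.80, g = 0.5: shift = −0.20 × 0.5 = −0.10.
- Low support, p = 0.60, g = 0.5: shift = −0.40 × 0.5 = −0.20.
- Spurious difference, high minus low: −0.10 − (−0.20) = +0.10, so high support looks 0.10 points worse than it is.

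| Completion, high / low | g | Spurious difference (high − low) |
|---|---|---|
| 80% / 80% | 0.5 | 0 |
| 80% / 60% | 0.3 | +0.06 |
| 80% / 60% | 0.5 | +0.10 |
| 30-point gap | 0.75 | +0.225 |
| 80% / 60% | −0.5 (healthier drop-outs) | −0.10 |

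**Bias over time within a group.** The same formula applies to a wave mean. If 20% of a group is missing at a late wave and they are 0.5 points worse, the observed mean is 0.20 × 0.5 = 0.10 lower than the true one, which resembles improvement. A stable level gap of this kind cancels in an analysis of within-patient change, where bias needs missingness related to change. It does not cancel in an analysis of wave means. The article leaves the time-series method open.

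**Power.** With 45 per cell, power = Φ(0.5 / (0.75 × √(1/n₁ + 1/n₂)) − 1.96).

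- 80% / 80% completion: n = 36 and 36, power 0.81.
- 80% / 50% completion: n = 36 and 22.5, power 0.70.

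**Usage measure.** 4 measurements × 3 CCQs = 12 requests per patient. If each produced a logged session, questionnaires would be 12/(12 + 12) = 50% of sessions for a patient with 12 voluntary log-ins, 12/(12 + 3) = 80% with 3, and 12/(12 + 48) = 20% with 48. Adding 12 to both arms turns 24 versus 12 into 36 versus 24: the difference stays 12 and the ratio falls from 2.0 to 1.5. With 90% and 60% questionnaire completion (assumed), it becomes 34.8 versus 19.2, and the difference itself moves from 12 to 15.6.

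**The case against.** The strongest reply is that the primary CCQ analysis is a time series within each care group, whereas the 0.10 belongs to the secondary support comparison. This stands: 0.10 is not a bias in the primary analysis. The planned 0.5 was derived from expected deterioration with and without the portal, not from a support contrast, so it gives scale only. The reply does not remove the exposure of the time series to selective loss.

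The design also partly intends to study users. The primary aim concerns portal use, and patients enter by agreeing to use it. That explains who is enrolled but does not excuse losing enrolled patients' outcomes afterwards.

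Several stronger readings are tempting but unsupported:

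- **Group 3 events are under-recorded.** The article says only that there is no active support. It also counts patient reports and says, without limiting this to groups 1 and 2, that care professionals can use the portal. Under-recording is plausible, not shown.
- **Log files no longer measure voluntary use.** The log metric is not defined, and a fuller plan may filter questionnaire sessions.
- **Repeated-measures ANOVA discards incomplete patients.** That holds only if it is run on complete cases, which the article does not say.
- **Pre-intervention CCQs need prior portal access.** The timing is in figures that are not available here. The CCQ planned for non-participants suggests that some collection outside portal use is possible.

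**Conclusion.** The concern holds for outcome capture. As written, the plan ties follow-up on the primary outcome to access to the portal, and use of the portal is what the randomised support is meant to change. Differential loss by support level is therefore a foreseeable consequence of the trial's own hypothesis, as is selective loss over time within a group. Complete-case repeated-measures ANOVA, if used, would add to it.

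The size is unknown. The 0.10 CCQ points rests on an assumed 20-point completion gap and an assumed 0.5-point deficit in non-completers. It is zero with equal completion and changes sign if healthier patients leave. The usage and group 3 recording effects are possibilities. A reader might infer that the CCQ, cost and usage results are all invalid; the documents do not support that.

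**What to change.** 1. Send the 12 CCQs, the EQ-5D and the MRC scale to every included patient by a direct e-mail link that needs no portal log-in, whether or not the patient uses the portal.
2. Analyse all randomised patients in 1a versus 1b and 2a versus 2b with a mixed model that uses all available data. This avoids complete-case loss but does not by itself cure missingness that depends on unobserved scores, so step 1 matters most.
3. Exclude questionnaire-driven sessions from the log-file usage counts.
4. Make no cost comparison of group 3 with groups 1 and 2 on portal-recorded care use. State that the 1a versus 1b and 2a versus 2b cost comparisons still depend on portal recording.

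The cost is a small survey set-up, a log-file filter and somewhat fewer portal visits prompted by the study. Internet access is already a condition of entry, and group 3 already receives log-in details by e-mail. Taking consultations and admissions from practice records in all three care groups would remove the remaining dependence, but it is not a small task and is not needed for this change.

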**Fig. 6 Fig6:**
[figure not shown]
ITS measurements per interval

### Outcome parameters

#### Primary outcome

The primary outcome is clinical and expressed as health status, measured using the CCQ. The CCQ was originally designed by Van der Molen and consist of 10 items with a 7-point Likert scale. The CCQ comprises 3 domains; symptom state (4 items), functional state (4 items) and mental state (2 items). Research showed that the CCQ is a reliable and valid questionnaire with Crohnbach’s alpha between 0.89 and 0.91 [29].

#### Secondary outcomes

From the human perspective we will measure the following outcomes:

##### Disability associated with breathlessness

This is measured using the Medical Research Council (MRC) breathlessness scale (see Appendix 2), which comprises five statements that describe almost the entire range of respiratory disability: from none (Grade 1) to almost complete incapacity (Grade 5). It can predict survival [32] and it is advocated as complementary to FEV_1_ in describing disability in those with COPD [33].

##### Quality of life (QoL)

QoL will be assessed using EuroQol-5D (EQ-5D). This questionnaire contains 5 items with a 3-point Likert scale. A higher score reflects higher quality of life. The EQ-5D comprises 5 levels: mobility, self care, daily activity, pain/discomfort and anxiety/depression. Research showed that the EQ-5D is a reliable and valid questionnaire [34]. The EQ-5D can be used to compute QALY’s, which are necessary to evaluate cost-effectiveness.

##### Adoption of the portal

Usage of the portal is monitored continuously by log files. User satisfaction is measured by purpose-designed questionnaires.

From the organisational perspective we will measure the following outcome:

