**Discussion:**

To our knowledge this is the first study to combine different study designs that enable simultaneous investigation of clinical effects, as well as effects of different organisational implementation methods whilst controlling for confounding effects of the organisational characteristics. We hypothesize that an implementation with higher levels of personal assistance, and integrated in an existing care program will result in increased use of and satisfaction with the platform, thereby increasing health status and diminishing exacerbation and hospitalisation.

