Because the most powerful studies are prospective studies, we chose a prospective parallel cohort design. We asked three primary care groups to invite their COPD patients for the e-Vita study. Because there are several differences between the groups (Fig. 3), we can not compare the COPD cohorts by combining data across three different groups. We chose for an interrupted time series (ITS) design to evaluate clinical outcomes (CCQ) within each group. In ITS studies, data are collected at multiple time points before and after an intervention in order to detect whether or not the intervention has a significantly greater effect than any underlying secular trend [26]. ITS can detect changes that are delayed or intermittent. It can also determine if the change is permanent or temporary. In addition, it allows evaluation of variables which are changing before the intervention, for instance, by comparing slopes of trend lines before and after the intervention. Finally, ITS makes it easier to control for confounding variables and regression to the mean [27]. The ITS will be performed according to guidelines of the EPOC Cochrane group [25]. Although well-conducted randomised trials provide the most reliable evidence on the effectiveness of interventions, they are not feasible for our setting of an implementation design with organisational changes in a real-life health care system within three different care groups with different demands. An advantage of an ITS design is that it allows for the statistical investigation of potential biases in the estimate of the effect of the intervention.

In addition to clinical outcomes, we also want to investigate the effect of different organisational implementation methods. Therefore we will implement the platform in group 1 and 2 using different methods. Differences will be measured using a parallel cohort design. To be certain that intervention groups will be balanced in known and unknown prognostic factors in the long run we will use randomisation within group 1 and 2. To rule out human influences we will randomise online for the level of support.

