### Data analysis

Along with our research design, analyses will be multilevel:To investigate the effect of the use of the web portal on the primary clinical outcomes, the ITS data will be analysed. The preferred method to analyse ITS studies is a statistical comparison of time trends before and after the intervention. Time series analysis using ARIMA models is one way of analysing the data, but there are a number of statistical techniques that can be used depending on the characteristics of the data, the number of data points available and whether autocorrelation is present. The final choice for the method to analyse the data will be made when the total set of data is available after consultation of a statistician.To investigate the effects of organisational aspects uptake of the portal will be analysed for care group 1, 2 and 3 using Chi Square tests (Fishers’ Exact Test for categorical variables and *F*-tests for continuous variables) and (repeated measures) ANOVA analyses. To analyse the effects of organizational aspects as described in the paper, the groups will be compared.To investigate the effect of integration of the web portal in daily practice, outcomes within integrated (group 1 and 2) and the free use groups (group 3) will be analysed using Chi Square tests (Fishers’ Exact Test for categorical variables and *F*-tests for continuous variables) and (repeated measures) ANOVA analyses.To investigate the effect of different organisational implementation methods, outcomes within groups with high level support (1a and 2a) and low level support (1b, 2b and 3) will be analysed using Chi Square tests (Fishers’ Exact Test for categorical variables and *F*-tests for continuous variables) and (repeated measures) ANOVA analyses.To explore correlation between self efficacy, sociodemographic characteristics on the one hand and adoption of the portal and clinical outcomes on the other hand, Pearson product-moment coefficients will be calculated across all research groups.To make a cost-effectiveness analysis, the direct costs of the different organisational implementation methods will be defined and analysed parallel to the effects of the portal in terms of Quality of Life (EQ-5D).

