## Discussion

COPD is one of the main causes of morbidity and mortality in the world. Worldwide nearly 3 million people die from COPD every year [1]. COPD is a highly complex disease to manage as patients show great variation in symptoms and limitations in daily life. An important treatment of COPD is empowerment of patients: self-management may reduce hospital admission and significantly improves health status [38]; it can diminish the impact of exacerbations on health status and tends to accelerate recovery [39, 40]. eHealth tools for COPD patients have potential to raise self-management to higher levels. Patients’ attitudes and receptiveness towards eHealth applications are promising [20] but lack of robust trials and inconclusive research results [17–20] make it impossible to draw firm conclusions about clinical effectiveness or cost effectiveness.

In this study we aim to empower COPD patients in primary care by providing a self-management web portal. We expect this portal to help patients to better recognize and self-manage exacerbations in an early phase, thereby increasing health status and diminishing exacerbation and hospitalisation. In addition we aim to provide practical insights into a successful implementation of patients portals in real-life primary care settings. We will therefore compare different organisational implementation methods. We expect that an implementation setup with greater personal support will result in increased use of the online program.

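### Satisfaction is collected through the portal, so patients who stop logging in are likely to be under-represented, probably unequally by support level, which biases the comparison against the arm with more users

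*Protocol article*

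**What the plan says.** Under Secondary outcomes, the entry on adoption of the portal pairs two measures. Use is recorded continuously by log files. For the other, "User satisfaction is measured by purpose-designed questionnaires", without stating who is asked, when, or by what route. The general rule is in the Data collection section: "Data collection consists of self reporting questionnaires that are integrated in the portal", followed by "Therefore all data collection is provided digitally".

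Use and satisfaction are the two outcomes of the second aim (Background). The Abstract predicts that more personal assistance, with integration into a care programme, "will result in increased use of and satisfaction with the platform". The main Discussion repeats the part on use: "We expect that an implementation setup with greater personal support will result in increased use of the online program".

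Support level is randomised only in two care groups: "in the long run we will use randomisation within group 1 and 2" (Methods/Design). The Data analysis section nevertheless states that "outcomes within groups with high level support (1a and 2a) and low level support (1b, 2b and 3) will be analysed", with chi-square or Fisher tests, F-tests and ANOVA. Group 3 is thus counted as low support, although it was not randomised and has a different portal.

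**The concern.** The intervention acts on the means of answering. In 1a and 2a a research nurse follows up by home visit or telephone and checks that the patient can log on. In 1b and 2b the patient gets a single demonstration and no follow-up. If the trial's hypothesis is right, more high-support patients will keep logging in, and more of them will meet the satisfaction questions.

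Portal collection affects the CCQ and the other questionnaires too. Satisfaction is more exposed because it rates the portal itself, so disliking the portal is a natural reason for not answering. Under low support the respondents would be mainly the patients whom the portal suits. Under high support they would also include hesitant patients who were kept in. The arm that retains more patients could then show too small an advantage in satisfaction, or none. Answers that were never requested from patients who left cannot be fully recovered by later analysis.

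**Working it through.** **Figures in the article.** There is none for satisfaction, for its response rate, or for use by support level. The Power calculation assumes 20% drop-out overall, not by support level. It plans 45 patients per implementation method: 90 + 90 + 45 = 225. The support contrast as planned is therefore:

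- high support (1a, 2a): 45 + 45 = 90
- low support (1b, 2b, 3): 45 + 45 + 45 = 135, of whom 45/135 = 33% are the non-randomised group 3

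**Selection model (all inputs assumed).** Let satisfaction have SD 1 in each arm over all randomised patients. A patient answers if a latent engagement variable, standard normal and correlated rho with satisfaction, exceeds a threshold that gives response share p. The mean among respondents then exceeds the arm's true mean by rho × φ(z_p)/p, where z_p is the standard normal quantile of p. The bias in the high-minus-low difference is

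rho × [φ(z_pH)/pH − φ(z_pL)/pL].

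The ratios φ(z_p)/p are:

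- p = 0.80: 0.280/0.80 = 0.350
- p = 0.70: 0.348/0.70 = 0.497
- p = 0.60: 0.386/0.60 = 0.644
- p = 0.50: 0.399/0.50 = 0.798

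Example, 80% v 50% with rho 0.5: 0.5 × (0.350 − 0.798) = −0.22 SD.

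Bias in SD:

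| Response, high v low | rho 0.3 | rho 0.5 | rho 0.7 |
|---|---|---|---|
| 80% v 80% | 0 | 0 | 0 |
| 80% v 70% | −0.04 | −0.07 | −0.10 |
| 80% v 60% | −0.09 | −0.15 | −0.21 |
| 80% v 50% | −0.13 | −0.22 | −0.31 |

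With rho = 0 the bias is zero at any response gap.

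**What would be observed.** Add the bias to a true benefit of high support, over the nine unequal-response cells.

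- True +0.10 SD: negative in six of nine, for example 0.10 − 0.15 = −0.05 at 80% v 60% and rho 0.5. One of the six (−0.003) is practically zero.
- True +0.20 SD: negative in three of nine. At 80% v 50% it appears as +0.07, −0.02 and −0.11 for rho 0.3, 0.5 and 0.7. The third is 80% v 60% at rho 0.7, practically zero (−0.006).
- True +0.30 SD: positive in eight of nine. The exception, 80% v 50% at rho 0.7, gives −0.01.

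**What a composite would show (rates assumed).** Suppose 80% still use the portal with high support and 80% of them are satisfied, against 50% and 90% with low support. Among users the result is 80% v 90%. Using and satisfied over all randomised patients is 0.80 × 0.80 = 64% v 0.50 × 0.90 = 45%. If use were 80% in both arms, the composite would be 64% v 0.80 × 0.90 = 72%. The change of direction comes wholly from the gap in use, which the log files measure anyway.

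**The case against.** The strongest objection is that the article nowhere says that only current users are asked. A reader might infer this from the portal route, but the text does not support it. A patient who no longer works on health goals may still log in to answer. The interrupted time series needs questionnaires before the intervention, so answering is not the same as continuing use. The article also plans CCQ data from non-participants, by a route that it does not describe, and the figure with the measurement schedule is not shown. This stands. The supportable statement is likely under-representation, not exclusion.

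A reader might also hold that satisfaction is conditional on use by definition, so that no other route could help. That does not follow: a patient who tried the portal and stopped can say that it did not suit. Only patients who never started lack a score by definition, and in groups 1 and 2 everyone is to begin with an instruction from the nurse.

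Three further objections have weight. Use is logged independently, so a gap in use would be visible beside the satisfaction result. Counting everyone who stopped as not satisfied assigns a value instead of measuring one. Invitations and the handling of non-response may be set in a full protocol or analysis plan. The last does not remove the point, because the portal route is stated in the article and no second route is given for satisfaction.

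**Conclusion.** The point holds as a risk of non-response that differs by arm in a secondary outcome, one of the two named in the second aim. It rests on three steps: the portal is the only stated route for satisfaction, support is expected to raise use, and engagement is assumed to correlate positively with satisfaction. The first two are in the article; the third is an assumption. Over response gaps of 10 to 30 points and correlations of 0.3 to 0.7, the bias is about −0.04 to −0.31 SD against high support. This understates a benefit and can reverse a small one, but over most of the range it would not reverse a moderate one.

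Two stronger conclusions are not supported. One is that the sign will reverse: this needs a small true effect with a sizeable gap and correlation, and the article gives none of these figures. The other is that the high v low contrast in the Data analysis section is a randomised comparison spoiled only by non-response. With group 3 in the low-support set, it would be confounded even with complete response. Selection after randomisation applies to 1a v 1b and 2a v 2b.

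**What to change.** - Use the log files to identify patients who have stopped logging in, and e-mail them the satisfaction items and a question on the reason for stopping, by a link outside the portal.
- State who is asked for satisfaction and when. Report response and use by arm next to the satisfaction result.
- Make the randomised comparison of support within groups 1 and 2 (1a v 1b, 2a v 2b), without group 3.
- Using and satisfied, over all randomised patients, may be added as a supportive analysis with both components shown. It need not be the main outcome.

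The cost is a little extra data collection. Patients without internet access are already excluded, and group 3 already receives log-in details by e-mail. For groups 1 and 2 the article does not say that e-mail addresses are held; if they are not, they could be recorded at intake. Some patients who stopped will still not answer, so the bias is reduced and not removed.
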